### Data collection

2.10

The general characteristics of the participants will be examined at the beginning of the study. Biochemical assays, disability status, quality of life, gastrointestinal symptoms, BMI, dietary intake, and physical activity will be evaluated at the beginning and end of the trial. Possible side effects of ginger supplementation will be monitored throughout the study. Laboratory assessments will be performed in Boghrat Pathobiology Laboratory, and nonlaboratory assessments will be done in Imam Reza (A.S) Clinic. Detailed data collection tools are presented below.

#### General characteristics

2.10.1

The general characteristics of MS patients will be collected through face‐to‐face interviews. These characteristics will include age, gender, marital status, level of education, occupation, duration of MS, number of MS relapses in the previous year, diseases other than MS, type and dose of MS medications, type and dose of other medications used, drug abuse, vitamin D supplementation, smoking habit, and alcohol drinking.

#### Biochemical assays

2.10.2

After 12 h of fasting, 10 ml of venous blood samples will be taken from the patients. Serum levels of neurofilament light chain, matrix metalloproteinase‐9, and interleukin‐17 will be measured by enzyme‐linked immunosorbent assay using ZellBio GmbH kits. Nitric oxide serum levels will be measured by colorimetric method using KiaZist kit. Complete and differential blood counts will be done using an automated hematology analyzer. Besides, a laboratory specialist will manually double‐check leukocyte differentials by examining blood smears under a microscope.

#### Disability status

2.10.3

The scores of disability status will be determined through examination by a neurologist ([name]) using EDSS. EDSS is a ranking scale used to standardize the severity and progression of MS. This scale evaluates the function of seven different systems including the pyramidal tracts, cerebellum, brainstem, tactile nerves, optic nerves, mental function, and enteric and bladder nerves along with the resulting disabilities, particularly in the area of walking. Its scores are in the range of 0−10, and higher scores indicate a greater severity of disability.^9^ It is worth mentioning that the minimal clinically important difference (MCID), the smallest amount of change in an outcome that may be considered important by clinicians or patients, for EDSS has been reported to be between 0.5 and 1.0 points.^36^

#### Quality of life

2.10.4

The scores of quality of life will be assessed using the self‐report questionnaire of MS Impact Scale (MSIS‐29), which has acceptable validity and reliability in Iranian patients.^37^ This questionnaire contains 29 items, 20 items of which measure the physical impact of MS and 9 items of which measure the psychological impact of MS on patients. Each item has 5 response options with a score of 1−5. Both physical and psychological scales are scored by summing the responses across the relevant items, then converting to a 0−100 scale. The higher the score the worse the quality of life.^38^ It is worth noting that the MCID for MSIS‐29 has been reported to be between 7.0 and 8.0 points.^39^, ^40^

#### Gastrointestinal symptoms

2.10.5

The frequency and severity of 12 gastrointestinal symptoms including anorexia, dysphagia, heartburn, nausea, vomiting, abdominal pain, bloating, belching, flatulence, constipation, diarrhea, and fecal incontinence will be evaluated using the self‐reported Visual Analog Scale (VAS) ranging from 0 (best) to 100 mm (worst). This method has been previously used by Preziosi et al. to assess gastrointestinal symptoms in MS patients.^41^ The MCID for VAS of gastrointestinal symptoms has been considered 10 mm.^42^

#### BMI

2.10.6

The participants' weight will be measured to the nearest 0.1 kg in light clothing without shoes using a calibrated digital scale. The participants' height will also be measured to the nearest 0.5 cm in the upright standing position without shoes using a stadiometer. Then, BMI will be calculated by dividing weight in kilograms by height in square meters.

#### Dietary intake

2.10.7

The usual dietary intake of each patient will be assessed using 3‐day food records. In this method, participants will write down the type and amount of their food intake during 2 weekdays and 1 weekend day. Then, a customized Nutritionist IV software will be used to convert food intake into energy and nutrients.

#### Physical activity

2.10.8

The usual physical activity of the participants will be assessed using the short form of the International Physical Activity Questionnaire, which has acceptable validity and reliability in Iranians.^43^ This questionnaire consists of 7 items, 6 of which are related to light (walking), moderate, and vigorous physical activity and 1 of which measures total daily sitting time. The level of physical activity will be calculated by multiplying the time allocated to each of the weekly activities by its metabolic equivalent (MET) and then summing the obtained scores. The unit of the total score is MET‐minutes per week. The METs of vigorous, moderate, and light physical activity are 8, 4, and 3.3, respectively.^44^

#### Possible side effects

2.10.9

Ginger consumption of up to 4000 mg per day is generally recognized as safe by the US Food and Drug Administration.^26^ However, given that the present study is the first RCT on the effect of ginger supplementation in MS patients, possible side effects of ginger or placebo tablets will closely be monitored during the study. This will be done according to the World Health Organization guidelines on safety monitoring of herbal medicines.^45^ Throughout the study, the patients will be encouraged to contact the principal investigator ([name]) if they suspect any complaint related to the intervention. In addition, the participants will be asked to report side effects and adverse events in weekly phone calls or text messages. Moreover, they will be interviewed for possible side effects (abdominal discomfort, heartburn, diarrhea, etc.) in face‐to‐face visits at the middle and end of the trial.

### Participant compliance

2.11

The participants will have face‐to‐face visits at the beginning, middle, and end of the study. In addition, adherence to the consumption of tablets will be monitored by weekly phone calls and text messages. Moreover, the subjects will be asked to record the number of consumed tablets by ticking a reminder table. Unused pills will also be taken from patients and counted at the end of the trial.

### Potential confounders

2.12

At the beginning of the study, multiple potential demographic and medical confounders will be recorded. Moreover, the participants in both groups will be asked to maintain their usual diet and physical activity pattern during the study period and to avoid consuming ginger and other products containing it. To ensure that the participants comply with the protocol, their dietary intake and physical activity will be assessed using the aforementioned tools at the beginning and end of the trial. Finally, all potential confounders will statistically be analyzed and if there is a significant difference between the groups, their effects on study outcomes will be adjusted.

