### Statistical analysis

2.13

SPSS Statistics software version 26 will be used for statistical analysis of data. The Shapiro–Wilk test and skewness will be applied to investigate the normal distribution of quantitative variables. Mean ± standard deviation or median [interquartile range] will be used to report quantitative variables, and number (percentage) will be used to report qualitative variables. For each outcome, the estimated effect size and its 95% confidence interval will be presented. The paired *t*‐test or Wilcoxon signed‐rank test will be performed to compare within‐group differences in quantitative variables. The independent *t*‐test or Mann−Whitney *U* test will be conducted to compare between‐group differences in quantitative variables. The analysis of covariance will be applied to compare between‐group differences by adjusting confounders. The Pearson *χ*
^2^ test or Fisher's exact test will be performed to compare between‐group differences in qualitative variables. All tests will be two‐tailed with a significance level of 0.05. The Statistical Analyses and Methods in the Published Literature (SAMPL) guideline will be followed for reporting statistical results.^46^

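### Section 2.12 adjusts for a covariate only if the randomised groups differ significantly on it, and the wording does not exclude diet and physical activity measured at the end of the trial

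*Protocol article*

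**What the plan says.** Section 2.12 of the protocol article (Potential confounders) proceeds in three steps.

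- Demographic and medical confounders are recorded at the start of the study.
- Participants are asked to keep their usual diet and activity, and "their dietary intake and physical activity will be assessed using the aforementioned tools at the beginning and end of the trial". The stated purpose is "To ensure that the participants comply with the protocol".
- The section closes with the rule itself, which opens with "Finally, all potential confounders will statistically be analyzed". The second half of that sentence sets the condition for adjustment: "if there is a significant difference between the groups, their effects on study outcomes will be adjusted".

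Section 2.10.1 lists the baseline items: "These characteristics will include age, gender, marital status, level of education, occupation, duration of MS, number of MS relapses in the previous year", followed by seven more on comorbidity, medication, drug abuse, vitamin D, smoking and alcohol, 14 in all. Section 2.13 gives an unadjusted comparison (the independent t-test or Mann-Whitney test "will be conducted to compare between‐group differences in quantitative variables") and an adjusted one: "The analysis of covariance will be applied to compare between‐group differences by adjusting confounders". It names no covariate, neither the baseline value of the outcome nor gender, which is the stratification factor in section 2.8. It adds: "All tests will be two‐tailed with a significance level of 0.05".

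**The concern.** The first problem is explicit in the text. In a randomised trial a baseline difference between the groups arises by chance, so its p-value carries no information on whether the covariate predicts the outcome. A strongly prognostic covariate that happens to be balanced is left out, and a weak one that happens to be unbalanced is put in. The reader cannot know the model until the data have been examined.

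The second problem is one of scope. The sentence on all potential confounders follows directly after diet and activity at both time points, and nothing limits it to baseline values. End-of-trial values are measured after randomisation and may be results of treatment. Section 2.10.3 says that the EDSS weighs walking in particular, and walking is scored in the activity questionnaire of section 2.10.8. Gastrointestinal symptoms, including anorexia and nausea, and BMI are outcomes closely tied to food intake. If such values were eligible, the rule would tend to adjust in just those trials where treatment had shifted them.

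**Working it through.** **Inputs.** Section 2.5 gives 22 per group before drop-out, two-sided alpha 0.05, and for the EDSS a difference of 0.74 with SDs 0.29 and 1.06. The documents give no correlation between covariate and outcome, so those below are assumptions shown as a range. The plan states no figure for the adjustment rule itself. Its sample size formula for the EDSS gives 10.507 × (0.29² + 1.06²) / 0.74² = 23.17, so 24 per group against the 22 stated. That is a separate matter; 22 is used here.

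**1. Chance imbalance.** Gender is stratified in blocks of 4, so a significant gender imbalance is practically excluded and 13 of the 14 items remain. If the tests were independent and exact at 5%, the chance of at least one significant result is 1 − 0.95^13 = 0.487, about 49%.

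**2. Baseline covariates.** Simulation with 22 per group, a true effect of 0 or 1 SD, and one baseline covariate with correlation ρ to the outcome:

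| ρ (assumed) | Power, always adjust | Power, protocol rule | Type I error, always adjust | Type I error, protocol rule |
|---|---|---|---|---|
| 0.3 | 92.3% | 90.6% | 0.052 | 0.050 |
| 0.5 | 95.6% | 90.9% | 0.049 | 0.043 |
| 0.7 | 99.5% | 91.1% | 0.046 | 0.034 |

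Power with no adjustment is about 90% throughout. The rule therefore recovers almost none of the available gain, and the test becomes slightly conservative. The estimate stays unbiased.

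**3. End-of-trial activity, if it were used.** The pooled SD is √((0.29² + 1.06²)/2) = 0.777, so the planned effect is d = 0.74/0.777 = 0.952 SD. Let activity be driven by the EDSS with within-arm correlation r. The adjusted effect is then 0.74 × (1 − r²), and the arms differ in activity by r × d SD. The normal approximation to the chance of triggering adjustment is Φ(r × d × √(22/2) − 1.96).

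- r = 0.5: adjusted effect 0.74 × 0.75 = 0.555. The shift is 0.476 SD, and Φ(1.58 − 1.96) is about 35% (34% to 35% by simulation).
- r = 0.7: adjusted effect 0.74 × 0.51 = 0.377. The shift is 0.667 SD, and Φ(2.21 − 1.96) is about 60% (58% by simulation with the t-test).

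Trials in which adjustment is not triggered have smaller than average unadjusted differences, by simulation about 0.676 and 0.590. The averages over all trials are therefore 0.35 × 0.555 + 0.65 × 0.676 = 0.63 and 0.58 × 0.377 + 0.42 × 0.590 = 0.47.

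**4. When treatment does not move the covariate.** In a second model, where diet lies on the path from treatment to outcome, a treatment effect of zero on diet gives a mean estimate of 1.01 against a true 1.0. That is no bias.

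**The case against.** The strongest reply concerns the end-of-trial half. A reader might infer that the plan will adjust for end-of-trial diet and activity. The text does not say so. Section 2.12 places the recording of demographic and medical confounders at the start of the study, gives compliance as the purpose of the repeated diet and activity measurement, and never states that end values enter the model. The time point of each covariate may also be settled in an analysis plan that is not shown. This stands: it is an ambiguity to close, not a stated error. It is a real ambiguity, because both time points sit in the confounder section immediately before the sweeping sentence.

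Three further limits also stand.

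- A reader might infer that the trigger inflates the type I error or biases the estimate through baseline covariates. It does neither; the test is slightly conservative.
- The figures 0.56 and 0.38 are not what the rule would yield on average. They apply only where adjustment is triggered.
- The 49% is an upper-end figure for the 13 items. Many are categorical and not independent of one another, and where Fisher's exact test is used, simulated rejection for a binary item at 26 per group is about 0.2% to 2.8%, not 5%. Testing nutrients from the diet records would add to the count, by a number the documents do not give.

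Section 2.13 does plan unadjusted tests as well, but it does not say which analysis is decisive. None of this rescues the significance trigger, which the article itself lays down. An analysis plan that followed it would inherit the fault.

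**Conclusion.** The point holds in two parts of different strength.

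**Stated in the text:** the significance trigger is inferior to prespecified baseline adjustment. It costs roughly 1 to 8 percentage points of power for a single covariate over assumed correlations of 0.3 to 0.7, and it leaves the model open until the data are seen.

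**Possible but not stated:** the wording lets end-of-trial diet and activity into the pool. Loss of part of the treatment effect then depends on three conditions: those values are used, treatment affects them, and the trigger fires. With r assumed at 0.5 or 0.7 and activity driven only by the EDSS, the planned 0.74 falls on average to 0.63 or 0.47. At r = 0.7 the estimate in triggered trials, 0.38, lies below the 0.5 to 1.0 range that section 2.10.3 gives as the minimal clinically important difference. The documents do not support a claim that this bias will occur. The plan should be changed because the remedy is simple and removes both problems.

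**What to change.** Replace the last sentence of section 2.12, and align section 2.13 with it, by a dated amendment made before unblinding:

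- Analyse each quantitative outcome by analysis of covariance that always includes the baseline value of that outcome and gender, plus any baseline prognostic factors named in advance.
- Drop the between-group significance test as a criterion for adjustment.
- State that no variable measured after randomisation is used as a covariate.
- Report end-of-trial diet and physical activity by arm, as compliance data.

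Section 2.2 describes the trial as in progress, so the date of the amendment relative to unblinding should be recorded. The cost is the rewording and the amendment itself; no new data are needed.

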### Statistical analysis

2.13

SPSS Statistics software version 26 will be used for statistical analysis of data. The Shapiro–Wilk test and skewness will be applied to investigate the normal distribution of quantitative variables. Mean ± standard deviation or median [interquartile range] will be used to report quantitative variables, and number (percentage) will be used to report qualitative variables. For each outcome, the estimated effect size and its 95% confidence interval will be presented. The paired *t*‐test or Wilcoxon signed‐rank test will be performed to compare within‐group differences in quantitative variables. The independent *t*‐test or Mann−Whitney *U* test will be conducted to compare between‐group differences in quantitative variables. The analysis of covariance will be applied to compare between‐group differences by adjusting confounders. The Pearson *χ*
^2^ test or Fisher's exact test will be performed to compare between‐group differences in qualitative variables. All tests will be two‐tailed with a significance level of 0.05. The Statistical Analyses and Methods in the Published Literature (SAMPL) guideline will be followed for reporting statistical results.^46^

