### Study aims

2.1

The main goal of this study is to determine the effect of supplementation with ginger on neurofilament light chain, matrix metalloproteinase‐9, interleukin‐17, nitric oxide, complete and differential blood counts, disability status, quality of life, gastrointestinal symptoms, and BMI in patients with relapsing‐remitting MS. The primary outcomes are interleukin‐17, nitric oxide, and disability status. The secondary outcomes are neurofilament light chain, matrix metalloproteinase‐9, complete and differential blood counts, quality of life, gastrointestinal symptoms, and BMI.

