### Sample size and sampling method

2.5

Given the study design and the existence of two independent groups, the following formula will be used to determine the required sample size:

$$n=\frac{{\left(Z_{1-\frac{\alpha }{2}}+Z_{1-\beta }\right)}^{2}\left(s_{1}^{2}+s_{2}^{2}\right)}{{\left(\mu_{1}-\mu_{2}\right)}^{2}}\;$$

Considering interleukin‐17 as one of the primary outcomes of this study, the number of samples in each of the intervention and control groups was determined to be 13 people (in total 26). The calculations were performed by assuming the type I error equal to 0.05 and the test power equal to 90% and by taking into account *S*
_1_ = 4.07, *S*
_2_ = 9.19, and the effect size equal to 9.28 based on the previous report.^30^

Considering nitric oxide as one of the primary outcomes of this trial, the number of samples in each of the intervention and control groups was determined to be 22 people (in total 44). The calculations were conducted by assuming the type I error equal to 0.05 and the test power equal to 90% and by taking into account *S*
_1_ = 0.72, *S*
_2_ = 0.19, and the effect size equal to 0.5 based on the previous report.^31^

Considering disability status measured by EDSS^9^ as one of the primary outcomes of the present study, the number of samples in each of the intervention and control groups was determined to be 22 people (in total 44). The calculations were done by assuming the type I error equal to 0.05 and the test power equal to 90% and by taking into account *S*
_1_ = 0.29, *S*
_2_ = 1.06, and the effect size equal to 0.74 based on the previous report.^32^

Finally, according to the maximum number of the samples (22 people in each group and 44 in total) and considering a drop‐out rate of ∼20%, the required sample size was estimated to be 26 patients in each group and 52 in total. The participants will be selected using convenience sampling method.

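### Section 2.13 plans within-arm significance tests of outcomes at 0.05, does not mark them as descriptive, and does not tie the effect size and its interval to the between-group contrast.

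*Protocol article*

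**What the plan says.** Section 2.13 (Statistical analysis) lists three kinds of test for quantitative variables:

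- Within arms, a paired t-test or the Wilcoxon alternative: "rank test will be performed to compare within"-group differences.
- Between arms, an independent t-test or the Mann-Whitney alternative: "test will be conducted to compare between"-group differences.
- Between arms with adjustment: "The analysis of covariance will be applied to compare between"-group differences, adjusting for confounders.

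One closing sentence sets the level for every test: two-"tailed with a significance level of 0.05". For each outcome, "the estimated effect size and its 95% confidence interval will be presented", with no statement of whether this is a change within an arm or a difference between arms.

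Two other sections bear on the point. Section 2.1 (Study aims) states the question: "The main goal of this study is to determine the effect of supplementation with ginger" on the listed outcomes. Section 2.5 (Sample size and sampling method) begins "Given the study design and the existence of two independent groups" and uses a two-sample formula for each of the three primary outcomes.

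**The concern.** A before-after test in the ginger arm compares patients with themselves. It makes no use of the placebo arm, so it gives up what randomisation and blinding were meant to secure. Anything that moves both arms over 12 weeks enters that test as if it were treatment effect: placebo response, the effect of regular contact with the study team, drift in the assays, a change of season.

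At stake is how the results are read. A significant change under ginger with a non-significant change under placebo is easily taken as efficacy, yet no difference between arms has been tested. Section 2.13 states both kinds of test at one level and does not say that the within-arm tests have a lesser role. The self-reported MSIS-29 and gastrointestinal scores are the likeliest to shift in both arms. They are secondary outcomes; the primary ones are interleukin-17, nitric oxide and a neurologist-rated EDSS.

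**Working it through.** **The plan's own figures.** The formula in section 2.5 is n = (z₀.₉₇₅ + z₀.₉₀)² (S₁² + S₂²) / difference², where (1.960 + 1.282)² = 10.507.

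| Outcome | S₁² + S₂² | Difference² | n per group | Stated |
|---|---|---|---|---|
| Interleukin-17 | 4.07² + 9.19² = 101.02 | 9.28² = 86.12 | 12.33, so 13 | 13 |
| Nitric oxide | 0.72² + 0.19² = 0.5545 | 0.5² = 0.25 | 23.31, so 24 | 22 |
| EDSS | 0.29² + 1.06² = 1.2077 | 0.74² = 0.5476 | 23.17, so 24 | 22 |

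The gap of two patients for nitric oxide and EDSS is a separate matter. What counts here is that the formula is for two independent groups, so the between-group contrast is what was powered. I use the plan's 22 evaluable patients per arm below.

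**What a within-arm test does when ginger has no effect.** Let both arms have the same true mean change c, in SDs of the change score, with normally distributed changes. The size of c is my assumption; the document gives none. The steps are:

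1. The paired t-test has 21 degrees of freedom, a two-sided critical value of 2.080, and noncentrality c√22. This is 1.41 at c = 0.3, 2.35 at c = 0.5 and 3.75 at c = 0.8.
2. The noncentral t distribution then gives p, the probability that the ginger-arm test is significant.
3. The arms are independent, so ginger is significant and placebo is not with probability p(1 − p).

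| Common change c | Ginger-arm test significant, p | Ginger significant, placebo not, p(1 − p) |
|---|---|---|
| 0 | 0.050 | 0.05 × 0.95 = 0.048 |
| 0.2 | 0.146 | 0.146 × 0.854 = 0.125 |
| 0.3 | 0.269 | 0.269 × 0.731 = 0.197 |
| 0.5 | 0.609 | 0.609 × 0.391 = 0.238 |
| 0.8 | 0.947 | 0.947 × 0.053 = 0.050 |

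With no common change, 0.048 counts both directions. Counting improvement only, it is 0.025 × 0.95 = 0.024.

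**Check by simulation.** In 100,000 simulated trials, the ginger-arm test was significant in 0.270 at c = 0.3 and 0.610 at c = 0.5. The split pattern occurred in 0.197 and 0.237. The between-group t-test was significant in 0.051, 0.050 and 0.049 at c = 0, 0.3 and 0.5, so it is unaffected by a common change. Among trials showing the split pattern at c = 0.3 or 0.5, close to nine in ten had a non-significant between-group test. The two planned analyses would then usually disagree.

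**Sensitivity to sample size.** With all 26 per arm, p is 0.313 at c = 0.3 and 0.688 at c = 0.5, and the split pattern has probability 0.215 in both cases.

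The split pattern does not rise steadily with c. It peaks near the middle of the range and returns to about 5% at c = 0.8, because the placebo arm also becomes significant.

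**The case against.** The strongest reply is that the article already points to the between-group contrast. The design is a parallel double-blind trial, the sample size uses a two-sample formula, and covariance adjustment is specified only for between-group comparisons. A single line fixing the level at 0.05 is a general threshold that also covers the tests on qualitative variables. It does not make every test an efficacy criterion. A reader might infer that the plan gives within-arm and between-group tests equal standing, or that the investigators mean to claim efficacy from a within-arm result. The document supports neither reading: it ranks no test, and it nowhere says that a within-arm change will be taken as an effect of ginger. This part of the reply stands.

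A second reply is that the deciding contrast is commonly named in an analysis plan, which is not shown. That would answer a complaint about silence alone. It does not answer the point that the article commits to within-arm significance tests and states their level.

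A third reply concerns size. Nothing in the document supports a common change of 0.3 to 0.5 SD. Some of it points the other way: no minimum score is required at entry, MS medication must have been stable for six months, patients must have been free of attacks and corticosteroids for three months, and a three-week run-in precedes allocation. This stands, and the percentages should be read as an illustration only.

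Finally, within-arm comparison has a fair use for dietary intake and physical activity, which section 2.12 measures at start and end to check that habits were kept. This also stands and limits the fix to trial outcomes.

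**Conclusion.** The point holds as a fault in what section 2.13 states. For trial outcomes it plans tests that cannot answer the question in section 2.1, leaves them unmarked as descriptive, and leaves the reported effect size and interval unattached to the between-group difference.

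The size is conditional. It assumes no ginger effect, 22 per arm, normal changes, and a common change of 0.3 to 0.5 SD that is not drawn from the document. On those terms, a significant ginger arm arises in about 27% to 61% of trials and the misleading split between arms in about 20% to 24%, against about 5% for the between-group test. Outside that range the split is rarer: about 2.4% in the direction of improvement (4.8% in both directions) with no common change, and about 5% at 0.8 SD.

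The valid between-group test is already planned, so this is a correction that should be made and not a flaw that undermines the trial.

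**What to change.** In section 2.13:

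- For trial outcomes, replace the within-arm tests by a description of each arm's change: mean or median change with its spread, and no p-value.
- Keep any within-arm comparison of dietary intake and physical activity, labelled as a compliance check only.
- State that efficacy conclusions, and the reported effect size with its 95% confidence interval, rest only on the between-group difference, adjusted for the baseline value of the outcome.

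Baseline values are already collected under section 2.10, so the change needs wording only: no new data and no change in sample size. The only downside is the loss of within-arm p-values.

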### Participant allocation

2.8

The patients will be assigned to the treatment and control groups using stratified permuted block randomization (block size = 4, allocation ratio = 1:1). The stratification will be done according to gender (female or male). The following valid website will be used for generation of random allocation sequence: https://www.sealedenvelope.com/simple-randomiser/v1/lists. Placebo and ginger tablets will be sealed in sequentially numbered identical bottles based on the allocation sequence. The sequence generation, allocation concealment, and assignment of the patients to the groups will be implemented by different trained persons. The participants, researchers, care providers, and outcome assessors will be blinded to the group assignment.

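### Covariate adjustment is triggered by a significant group difference, so baseline outcome values would rarely be adjusted for and sex practically never; a prespecified baseline-adjusted ANCOVA is at least as precise at almost no cost

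*Protocol article*

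**What the plan says.** Four parts of the protocol article bear on this.

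- **Statistical analysis (2.13).** Between-group differences in quantitative variables are tested by independent t-test or Mann-Whitney U test, without covariates. The next sentence begins "The analysis of covariance will be applied to compare" and provides for adjustment for confounders. No covariate is listed, neither analysis is called primary, and the text does not say whether the t-test is on week-12 values or on change. Tests are two-sided, "with a significance level of 0.05".
- **Potential confounders (2.12).** The variables described are demographic and medical factors recorded at the start, plus diet and physical activity. Their effects are adjusted for only when the groups differ significantly on them.
- **Data collection (2.10).** The list "Biochemical assays, disability status, quality of life, gastrointestinal symptoms, BMI" is assessed at both the start and the end, so every outcome has a baseline value.
- **Participant allocation (2.8).** Randomisation is 1:1 in blocks of four. "The stratification will be done according to gender (female or male"). Sex is also among the general characteristics recorded (2.10.1).

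**The concern.** Two variables have a claim to be in the model from the outset: the baseline value of the outcome, usually its strongest predictor, and the stratification factor, which is part of the design. The rule in 2.12 admits a covariate only through a significance test of group balance. Randomisation makes such a test fire for a baseline outcome value at about its nominal rate, and blocking within sex makes it practically impossible for sex. The adjustment the plan offers would therefore seldom be used where it helps.

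What is at stake is precision, together with clarity about which result counts. The trial is small, and on its own planning inputs it has less than the 90% power it aims for. With adjusted and unadjusted tests both listed and neither ranked, each of the three primary outcomes could also yield two results.

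**Working it through.** **Inputs from section 2.5.** Two-sided alpha 0.05; "the test power equal to 90"%; nitric oxide S1 = 0.72, S2 = 0.19, difference 0.5; EDSS S1 = 0.29, S2 = 1.06, difference 0.74; 22 per group before drop-out, 26 after allowing about 20%. The correlation r between baseline and week 12 is not given; I assume 0.3 to 0.8.

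**1. The plan's own figure.** n = (1.960 + 1.282)² (S1² + S2²) / difference².
- Nitric oxide: 10.507 × 0.5545 / 0.25 = 23.3, so 24 per group.
- EDSS: 10.507 × 1.2077 / 0.5476 = 23.2, so 24 per group.

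The stated 22 is not reproduced. That is a separate matter; it is relevant here only because it shows there is no precision to spare. For both outcomes, power at 22 per group is about 88% (normal approximation) or 87% (t distribution).

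**2. How often the rule would adjust.**
- Baseline outcome value: under randomisation, a test at 0.05 is significant about 5% of the time.
- Sex: with blocks of four, the arms differ by at most 2 within each sex. Over the splits possible at N = 52 with at least 8 of each sex, the most unequal is 3 v 5 in one sex and 23 v 21 in the other, chi-square p = 0.44. So at randomisation sex would not meet the trigger.

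**3. Variance ratios.** With equal variances at the two times and a common slope, and taking the week-12 variance as 1, the change score has variance 2(1 − r) and ANCOVA has 1 − r². ANCOVA relative to change is then (1 − r²) / [2(1 − r)] = (1 + r)/2.

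| r (assumed) | ANCOVA / week-12 t-test | ANCOVA / change t-test |
|---|---|---|
| 0.3 | 0.91 | 0.65 |
| 0.5 | 0.75 | 0.75 |
| 0.7 | 0.51 | 0.85 |
| 0.8 | 0.36 | 0.90 |

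**4. Power for nitric oxide at 26 × 0.8 = 20.8 per group.** This assumes the planning SDs are of week-12 values.
- Unadjusted: 0.5 / √(0.5545/20.8) = 3.062; Φ(3.062 − 1.960) = 86.5%.
- ANCOVA, r = 0.3: 3.062/√0.91 = 3.210; power 89.4%.
- ANCOVA, r = 0.5: 3.062/√0.75 = 3.536; power 94.2%.

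If the SDs are instead of changes, r = 0.9 gives 3.062/√0.95 = 3.142, power about 88%.

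**5. What the trigger rule recovers.** Simulation with the EDSS difference, a common SD of 0.777 and 22 per group (4,000 runs for power, 8,000 under the null). The trigger rule is applied to the week-12 t-test.

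| r | t-test, week 12 | t-test, change | ANCOVA always | Adjust only if baseline differs | Type I error of that rule |
|---|---|---|---|---|---|
| 0.3 | 86.1% | 73.5% | 88.8% | 86.3% | 5.1% |
| 0.5 | 87.6% | 87.1% | 94.5% | 88.3% | 4.3% |
| 0.7 | 87.0% | 98.0% | 98.9% | 88.8% | 3.6% |
| 0.8 | 86.8% | 99.7% | 99.9% | 88.8% | 2.9% |

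The rule recovers little of the available gain, and its type I error falls below nominal as r rises.

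**The case against.** The strongest reply is that the article leaves matters open rather than deciding them badly. It does provide an ANCOVA, it calls no test primary, and a covariate list may properly sit in a SAP or fuller protocol. That stands as far as the missing list goes. It does not cover the trigger in 2.12, which the article states as a rule and which would govern whatever list is used.

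Several stronger readings are tempting, and the documents do not support them.

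- **That the main analysis ignores baseline.** No main test is named, and the t-test may be on change, which uses baseline. The gain from ANCOVA is then smaller and shrinks as r rises: in the simulation at r = 0.7, 98.0% against 98.9%. A stable outcome such as EDSS is the worst case only if week-12 values are compared.
- **That chance imbalance biases the estimate.** Over repeated randomisation the unadjusted difference is unbiased; chance imbalance is part of its sampling variance. Only bias conditional on the observed imbalance could be argued.
- **That omitting sex makes standard errors too wide.** This holds only if sex predicts the outcome, and nothing in the article shows that it does.
- **That ANCOVA makes good the sample-size shortfall.** It passes 90% at r = 0.5 with week-12 SDs, but not at r = 0.3, nor with change-score SDs at r = 0.9. Section 2.5 gives no correlation and does not say which kind of SD it uses. The nitric oxide SDs also differ 3.8-fold between groups (0.72/0.19), so a common slope is only an approximation.

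It is also fair to say that a linear model may suit neither EDSS, which the article describes as a ranking scale, nor symptom VAS scores if many are zero.

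**Conclusion.** The point holds as a defect in the covariate rule and as an improvement available at almost no cost. It is not a validity failure: the unadjusted comparison is unbiased under randomisation, and in the simulation the trigger rule kept type I error at about 5% or lower.

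That the rule would rarely admit baseline values and practically never sex follows from the stated design and needs no assumption about r. The size of the loss does depend on r, on whether the t-test uses week-12 values or change, and on which SDs the planning figures represent. For r between 0.3 and 0.8, baseline-adjusted ANCOVA removes 9% to 64% of the variance of a week-12 comparison, or 35% to 10% of that of a change-score comparison. The gain from sex cannot be quantified; the reason to include it is that the analysis should match the stratified randomisation.

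**What to change.** In 2.13, state that the primary between-group analysis of each primary outcome, and of other quantitative outcomes where the model is suitable, is ANCOVA of the week-12 value on treatment, the baseline value of that outcome and sex, fitted whatever the baseline comparisons show. In 2.12, delete the rule that selects covariates by a significant group difference. Log-transform skewed biomarkers. Where a linear model does not fit, for example EDSS or VAS scores with many zeros, use a rank-based or ordinal analysis that still adjusts for baseline. Keep the t-test or Mann-Whitney test as a sensitivity analysis, and say whether it is on week-12 values or on change.

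The cost is a few sentences, two degrees of freedom and slightly more analysis work. No new data or patients are needed.
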